#### Data Analysis

The effectiveness of FOCUSau will be compared with the standard care (control group) for each participant population (patients or caregivers). Our hypotheses will be tested using a mixed model (per participant population) with the T_1_ measurement values for emotional well-being and self-efficacy as primary outcomes using a significance level of α=.025. These mixed models will be implemented using SPSS (IBM Corp) for Windows (version 27.0; Microsoft Corp) and R (R Core Team) with the recruitment centers treated as a random effect and the randomization groups as predictor variables. As per the FS procedure, the null hypotheses of the second primary end point (self-efficacy) will only be tested if a significant result is found for the first primary end point (emotional well-being). Additionally, we will incorporate other factors identified in the literature as potentially predictive by including them as covariates in the mixed models. We will perform analyses on both “intention-to-treat” and per-protocol principles. To interpret the magnitude of the effects for the different outcomes, we will estimate effect sizes (Cohen *d*). Our analysis will encompass all primary and secondary outcomes. Primary end points, including emotional well-being and self-efficacy measured at T_1_, will be analyzed first. Following that, secondary end points, comprising outcomes measured at T_1_ that are not primary end points, as well as all outcomes measured at T_2_ (occurring 24 weeks from T_0_), will be assessed. This approach allows for a comprehensive evaluation, including the examination of longer-term effects.

The robustness and validity of the results will be explored using sensitivity analyses by varying the parameter inputs (including sensitivity to the use of values for missing observations). The analysis will be conducted within trial period; the potential to extrapolate results over the longer term will be assessed based on the proportion of patients alive at the end of follow-up.

For the cost-effectiveness analysis, costs will be reported as the mean costs of care per dyad in each arm of the study. Costs applied to health care service use will be as per Australian standard fees (eg, via the Medicare Benefits Schedule). If a difference in outcomes is observed, as hypothesized, the incremental cost-effectiveness of FOCUSau compared with control will be estimated in terms of the (1) cost per additional patient with a meaningful improvement in emotional well-being (as assessed using the EORTC QLQ-C30 emotional well-being scale) and separately, and (2) cost per additional caregiver with a meaningful change in self-efficacy (as assessed using the Lewis’ Cancer self-efficacy scale). The base case analysis of cost-effectiveness will be conducted from a health care system perspective. Subsequent sensitivity analyses will modify the assessment of costs to adopt a societal perspective to capture the impact of informal care costs, as well as test the robustness of the analysis results to variations in other parameter inputs.

Missing data for costs and outcomes will be described and summarized. Where missing data can be regarded as missing at random, likelihood (interpolation) methods will be used for the analysis of those data as appropriate.

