#### Sample Size

A predetermined strict fixed sequence (FS) procedure defines prospectively hierarchical ordering of the primary end points; (1) emotional well-being and (2) self-efficacy. Testing of null hypotheses proceeds according to their hierarchical order; that is, H(1)0 is tested first at a significance level of 5%, and if H(1)0 is rejected then H(2)0 is tested at the same significance level, otherwise H(2)0 is not tested at all. The strict FS approach has the highest power for testing the first hypothesis (outcome: emotional well-being) compared to the other methods, as it does not save any portion of α for testing the later hypothesis. The reference mean value from EORTC for all patients with cancer, stage III-IV is 71.5 (SD 23.8). To maintain rigorous control over type I errors due to multiple comparisons, the α level is set at .025 instead of the more common .05. This adjustment accounts for the multiple comparisons required in the study, including comparisons between a control group and 2 participant groups (patients and caregivers). We set the statistical power at 0.80. The expected difference between the control group and the intervention arm in the primary outcomes is SD 0.375 at T_1_ (12 weeks). With these parameters, 173 dyads are needed in each arm (ie, 346 dyads in total). Anticipating a maximum 80% retention rate at T_1_ (US FOCUS retention was 86% [38]) we will require approximately 433 dyads to be recruited. An enrollment rate of 55% of those eligible was achieved in a prior digital health FOCUS study from 2014 [38]; however, we anticipate this will be higher for FOCUSaus (estimating 70%) given the internet is much more widely available now and our digital recruitment approach, meaning that we will need to identify approximately 618 dyads who meet eligibility criteria. Evidence also suggests that recruitment rates can increase when a digital health intervention is offered [18]. To meet these targets the CTS has calculated that approximately 6 referral sites will be required complemented by our aforementioned self-referral strategy.

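### The .025 split between patients and caregivers is valid but passes no alpha between them, which costs some power, and it conflicts with a 5% level stated in the same section

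*Protocol article*

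**What the plan says.** Two sections of the protocol article bear on this, both under Stage 2.

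- **Sample Size, fixed sequence.** Emotional well-being comes first and self-efficacy second. The text says that "H(1)0 is tested first at a significance level of 5" percent, and then: "if H(1)0 is rejected then H(2)0 is tested at the same significance level, otherwise H(2)0 is not tested at all".
- **Sample Size, alpha.** A few sentences later, "the α level is set at .025 instead of the more common .05". The reason given is multiplicity, "including comparisons between a control group and 2 participant groups (patients and caregivers").
- **Data Analysis.** One mixed model is fitted per participant population, with the 12-week values for "emotional well-being and self-efficacy as primary outcomes using a significance level of α=.025". The section repeats that self-efficacy is tested only after a significant result for emotional well-being.

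Neither section describes a transfer of alpha from one population to the other, and neither expressly excludes it. The article does not say whether the gate to self-efficacy works within each population or across both. I read it as within each, because the models are fitted per population. Sidedness is not stated, and I take the tests as two-sided.

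**The concern.** There are two linked problems.

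1. **Two alpha levels for the same first test.** Under the 5% wording, *the same significance level* for self-efficacy also means 5%. Under the later wording and the Data Analysis section it is .025. Which level governs decides whether the trial controls family-wise error at 5%.
2. **Unused alpha under the .025 reading.** This is a Bonferroni split across two populations with a fixed sequence inside each. Once both endpoints in one population are rejected, its .025 has no further use, although it could validly pass to the other population. Sample Size defends the strict fixed sequence on grounds of power, because it holds back no alpha for the later hypothesis. Leaving .025 idle across populations sits poorly with that reasoning.

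At stake are the confirmatory claims in the weaker population, and self-efficacy above all, since it is reached only through emotional well-being. The trial's first hypothesis concerns both outcomes in patient-caregiver dyads, so winning in both populations matters.

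**Working it through.** **Inputs from Sample Size:** effect 0.375 SD, alpha .025, power 0.80, 173 analysed dyads per arm. **Assumed, because the article does not give them:** two-sided tests, 0.375 SD on all four tests, correlation 0.3-0.5 between endpoints, correlation 0.2-0.3 within dyads.

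**1. The plan's own figure.** n per arm = 2(z₀.₉₈₇₅ + z₀.₈₀)²/0.375² = 2(2.2414 + 0.8416)²/0.1406 = 135.2, so 136 (137 by the t-test). The stated 173 is not reproduced. That is a separate question, but it is why results are shown at both 173 and 137 per arm.

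**2. Power of one test of emotional well-being at 173 per arm.** Noncentrality is 0.375·√(173/2) = 3.488.

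- At .025: Φ(3.488 − 2.241) = 0.894.
- At .05: Φ(3.488 − 1.960) = 0.937.

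Passing alpha on therefore cannot add more than 0.937 − 0.894 = 4.3 points for emotional well-being at this size.

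**3. The 5% reading.** With 5% in each population, family-wise error is 1 − 0.95² = 9.75% if the two are independent, and at most 10%.

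**4. Why the transfer keeps 5%.**

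- If true nulls lie in one population only, that population's sequence is tested at .05 at most. An error requires rejecting its first true null, so the error is at most .05.
- If true nulls lie in both populations, alpha can move only after both endpoints of one population are rejected, and those include a true null. Until the first false rejection both sequences run at .025, so the error is at most .025 + .025 = .05.

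Every rejection under the split is also made under the transfer rule, so at the 5% family-wise level the split is dominated.

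**5. Simulated power** (four correlated normal test statistics, at least 400,000 runs):

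| Analysed per arm | Claim | Split | With transfer | Gain (points) |
|---|---|---|---|---|
| 173 | Emotional well-being | 0.89 | 0.93 | about 3 |
| 173 | Self-efficacy (both steps passed) | 0.81-0.82 | 0.87 | 5-6 |
| 173 | All four | 0.67-0.70 | 0.78-0.80 | 10-11 |
| 137 | Emotional well-being | 0.81 | 0.85 | about 4 |
| 137 | Self-efficacy (both steps passed) | 0.67-0.70 | 0.74-0.76 | 6-7 |
| 137 | All four | 0.48-0.52 | 0.61-0.64 | 12-13 |

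Gains are taken before rounding. For example, emotional well-being at 173 per arm goes from 0.894 to about 0.925.

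**6. Sensitivity.**

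- *Wider correlations* (dyad 0-0.8, endpoint 0-0.6), 173 per arm: gains of 2.1-3.6 points for emotional well-being and 3.6-6.3 for self-efficacy.
- *Caregiver effect 0.20-0.25 SD*, 173 per arm: about 0.4-2 points for patients and 8-10 for caregivers.
- *No caregiver effect*: patients gain nothing.

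**7. Simulated error.** Under the global null, both rules give about 4.9% at dyad correlation 0 and 4.1% at 0.8. When only patients benefit (0.375 SD, 173 per arm), the caregiver false-positive rate is 2.5% with the split and about 4.5% with transfer. It approaches 5% only as patient power nears 1.

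**The case against.** The strongest reply is that nothing here is broken. A Bonferroni split with a fixed sequence inside each population is a valid, conservative rule, and the article gives its reason. At 173 analysed per arm it delivers 0.89 for emotional well-being and 0.81-0.82 for self-efficacy under the assumptions above, both over the stated 0.80. The article sets no power target for winning all four tests. It is also silent on transfer, and the full rule may be in an analysis plan that is not shown. All of this stands, and it limits the point to an improvement.

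A second reply is that the split holds each population's own false-positive rate at 2.5%, which transfer gives up. That also stands as a real cost. A reader might infer that the split brings no gain in error control at all. This is true of the 5% family-wise bound but not of the per-population rate. Still, the article's stated reason for .025 is multiple comparisons, not a 2.5% standard for each population.

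A third reply is that the size rests on effects and correlations the article does not give. It does. A reader might also take the upper figures as a loss of up to 7 points on every primary endpoint. That is not supported: in the equal-effects case, gains near 7 arise only for self-efficacy at about 137 per arm, and emotional well-being at 173 cannot gain more than 4.3.

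None of these replies removes the conflict between 5% and .025, which is in the text itself.

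**Conclusion.** The point holds as an efficiency gain together with a contradiction to be resolved. The article states both 5% and .025 for the first primary test, and the first level, used in both populations, would allow family-wise error near 10%. Under the .025 reading the rule is valid but dominated at the 5% family-wise level. With 0.375 SD on all four tests and the assumed correlations, the power given up at 173 per arm is about 3 points for emotional well-being, 5-6 for self-efficacy and 10-11 for all four. The loss is somewhat larger at 137 per arm and nil for patients if caregivers do not benefit. A reader should not conclude that the primary tests are invalid, that the planned 173 per arm misses its power target, or that the article expressly forbids transfer. The documents support none of these.

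**What to change.** State one procedure, worded identically in Sample Size and Data Analysis, and remove the 5% wording for the first hypothesis:

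- Patients and caregivers each start at two-sided .025.
- Within each population, emotional well-being is tested first, and self-efficacy only if emotional well-being is rejected.
- If both endpoints in one population are rejected, its .025 passes to the other population, whose sequence is re-tested at .05.

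If the sponsor prefers to hold each population at 2.5%, the split can stay. The text should then say so, and the 5% wording must still go.

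**Cost.** No further dyads or data are needed. Recruitment began in July 2024, so the change requires a documented, justified amendment before unblinding. The statistical price is that a population's own error rate can rise from 2.5% to at most 5%.

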#### Data Collection: Primary and Secondary Psychosocial Outcomes

Patient-caregiver dyad data will be collected at 3 time points—baseline (T_0_) completed prerandomization, first follow-up (T_1_) at 12 weeks post baseline, and second follow-up (T_2_) at 24 weeks post baseline. All data will be completed by the dyads (regardless of allocation) using the FOCUSau software platform, whereby they will complete a suite of internet-based questionnaires. The platform enables the application of data validation rules to ensure that required data are entered or that an annotation is provided to explain any missing data. The FOCUSau platform automatically generates a unique ID number used by the dyad to log into the platform. Data collection will be completed separately by the patient and caregiver (regardless of allocation). The data collection points, outcomes, and measures have been selected in accordance with those used in the aforementioned EU trial to enhance international comparison and potential generalizability [39].

The list of variables and associated measures to be completed by the dyad are summarized in Table 1 and are as follows, for the primary outcomes—emotional well-being (10 items describing emotional functioning from the European Organization for Research and Treatment of Cancer (EORTC) The European Organisation for Research and Treatment of Cancer Core Quality of Life Questionnaire (QLQ-C30) [55,56] and self-efficacy (The Lewis’ Cancer self-efficacy scale [57]); for the secondary outcomes—QoL of patients—EORTC QLQ-palliative care [58], 2 social functioning items (#26, 27) plus 1 item about overall health (#29) from the EORTC QLQ-C30, social well-being scale from Functional Assessment of Cancer Therapy-General (FACT-G)—and family caregivers (The Caregiver Quality of Life Index-Cancer [59]), appraisal of illness (Benefits of illness scale [60]), coping (Brief cope [61]), and dyad communication (Ways of giving support questionnaire [62] plus 1 item from the Dyadic Coping Inventory).

In addition, we will administer a sociodemographic questionnaire at baseline (T_0_) and a modified version of the Eastern Cooperative Oncology Group (ECOG) Performance Status Assessment [63] (response option 5 “death” removed as not relevant for this study).

**Table 1 table1:** Trial data collection measures.

Objective and outcome or variable			Instrument	Timing		
				T_0_: Before randomization	T_1_:T_0_ + 12 weeks	T_2_: T_0_ + 24 weeks

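### The primary model does not commit to the T0 value of the same outcome as a covariate, although every dyad supplies it before randomisation

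*Protocol article*

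**What the plan says.** The Data Analysis section of the protocol article specifies one mixed model per participant population. The response is the value at T1, not the change from T0. The terms are given as "with the recruitment centers treated as a random effect and the randomization groups as predictor variables", and the T1 values serve "as primary outcomes using a significance level of α=.025". The same paragraph then says that "we will incorporate other factors identified in the literature as potentially predictive by including them as covariates in the mixed models". No variable is listed there, and the T0 score is not mentioned as a covariate anywhere in the article.

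The baseline score is available. The data collection section has "baseline (T_0_) completed prerandomization", and Allocation and Blinding places randomisation after the baseline measures are complete. Table 1 ticks T0, T1 and T2 for emotional well-being and for self-efficacy, with the same instruments at each time, in patients and in caregivers. Randomisation is described as blocked, and no stratification is mentioned. The Sample Size section refers to no baseline correlation.

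**The concern.** For a questionnaire score measured twice in the same person, the earlier score is usually among the strongest predictors of the later one. A model for the T1 value that omits it leaves predictable between-person variation in the residual. The confidence interval is then wider than it need be, and a chance difference between arms at T0 carries into the estimate.

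This matters here because the endpoints are tested in sequence: self-efficacy is tested only if emotional well-being is significant, so power lost on the first endpoint also limits the second.

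The covariate sentence does not settle the matter. A model with T0 and a model without it both fit the text, so the article leaves open which one gives the primary p-value.

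**Working it through.** **Inputs from the Sample Size section.** Alpha: "the α level is set at .025 instead of the more common .05". Power: "We set the statistical power at 0.80". Expected difference: 0.375 SD at T1. Planned number: 173 dyads per arm, 346 in total, with 433 recruited to allow for 80% retention. Sidedness is not stated; two-sided is assumed.

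**Input not in the document.** The T0–T1 correlation r within arm. It is assumed to be 0.3, 0.5 or 0.7.

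**Step 1: the plan's own figure.** Per arm, n = 2(z₁₋α/₂ + z_power)² / d² = 2 × (2.241 + 0.842)² / 0.375² = 2 × 9.505 / 0.1406 ≈ 135.2, so 136 (137 by the t test). The stated 173 does not follow from the stated inputs. That is a separate matter and does not decide this one. The attrition step does reproduce: 346 / 0.8 = 432.5, so 433. Since 173 per arm is the number the plan intends to have at T1, it is used below.

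**Step 2: power without T0 at 173 per arm.** The standard error of the difference, in SD units, is √(2/173) = 0.1075. Then 0.375 / 0.1075 = 3.488, and power = Φ(3.488 − 2.241) = Φ(1.246) = 89.4%.

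**Step 3: power with T0 as covariate.** The variance of the treatment effect is multiplied by 1 − r², so the standard error is multiplied by √(1 − r²). Power = Φ(3.488 / √(1 − r²) − 2.241). The detectable difference at 80% power is (2.241 + 0.842) × √(1 − r²) × 0.1075.

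| Assumed r | Variance factor | Variance cut | Interval narrower by | Power at 173 per arm | Detectable difference |
|---|---|---|---|---|---|
| no T0 | 1.00 | – | – | 89.4% | 0.331 SD |
| 0.3 | 0.91 | 9% | 5% | 92.1% | 0.316 SD |
| 0.5 | 0.75 | 25% | 13% | 96.3% | 0.287 SD |
| 0.7 | 0.51 | 51% | 29% | 99.6% | 0.237 SD |

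These are two-group calculations by the normal approximation. They ignore the centre effect and compare with a model that has no other covariates.

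**Step 4: chance imbalance.** With 173 per arm, the standard error of the difference in T0 means is also about 0.11 SD. A T0 difference of 0.2 SD is therefore roughly a two-standard-error event. At r = 0.5 it would move an unadjusted T1 estimate by 0.5 × 0.2 = 0.1 SD, which is 0.1 / 0.375 = 27% of the target difference.

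**The case against.** The sentence on literature-based factors means that the model is not confined to group and centre. A reader who stops at the random-effect clause might infer that it is, and that the trial will not adjust for baseline. The document does not support either inference. The T0 score fits naturally among predictive factors, and a full protocol or analysis plan that is not shown may name it.

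A reader might also infer that covariates will be picked once results are visible. The article does not say so. It gives the literature as their source, and Allocation and Blinding keeps the research team blind to arm until the final data-collection point.

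Nor is an analysis without T0 biased. Randomisation protects it over repeated trials, and a chance imbalance is part of its sampling error.

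The size is open to challenge too. It depends wholly on an assumed correlation; at r = 0.3 the gain at 173 per arm is under 3 percentage points, and unadjusted power is already above the 0.80 target. Other prognostic covariates could take up part of the gain.

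All of this stands, and it limits the point to one of precision and clarity. What remains is that the article chose to state the outcome, the random effect, the predictor, the alpha and a covariate rule, yet does not commit to the one covariate that is certain to be available for both primary outcomes in both populations.

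**Conclusion.** The point holds as a loss of efficiency that costs almost nothing to avoid. The stated model neither includes nor excludes the T0 value of the same outcome. If T0 is left out, the treatment effect stays unbiased, but its variance is larger than necessary: adjustment would cut it by 9 to 51% for assumed correlations of 0.3 to 0.7. Power at the planned 173 per arm would go from 89% to between 92% and 99.6%, with 96% at r = 0.5. These figures assume a two-sided alpha of .025, a true difference of 0.375 SD and no other prognostic covariates in the model. The documents do not support a claim that the analysis is invalid, or that baseline adjustment has been ruled out.

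**What to change.** State in the Data Analysis section that each T1 and T2 outcome with a T0 value is modelled on randomised group, with the T0 value of the same outcome as a covariate and recruitment centre as a random effect. Name any further covariates before allocation is unblinded; they may stay in the primary model, as the article intends, provided the list is fixed by then. If an analysis plan already says this, the article needs only a matching sentence. The cost is a sentence or two of text. The T0 data are already being collected, and neither trial conduct nor the sample size has to change.

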### Research Aim and Hypotheses

We seek to determine the effectiveness and maintainability of a digital health intervention (iFOCUS) aimed at improving the well-being of patients with advanced cancer and their primary family caregivers. Our objectives are to (1) adapt iFOCUS to the Australian context to create FOCUSau; (2) examine the effectiveness of FOCUSau in improving the well-being (primary outcomes are emotional well-being and self-efficacy) of patients with advanced cancer and their primary family caregiver, compared to the control group (usual care); (3) compare the types and costs of health services used by participants in the intervention and control group; and (4) assess the acceptability, feasibility, and scalability of FOCUSau in order to inform the maintainable implementation of the intervention within the Australian health care system.

Our hypotheses are that compared to the control group, patent-caregiver dyads in the intervention group (who receive the intervention in addition to usual care) will, at 12 weeks follow-up, report (1) higher levels of emotional well-being and self-efficacy (ie, confidence in managing illness; primary outcomes) and (2) higher QoL, less negative appraisal of illness or caregiving, better communication about the illness, and improved coping ability (secondary outcomes). In addition, FOCUSau will be cost-effective compared with the control group in terms of the incremental cost (change in health care use) per additional participant with a meaningful change in (1) emotional well-being and (2) self-efficacy.

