	**Cost-effectiveness**					
		Health economic measures	For patients (23 items) 17 and for caregivers (14 items): client Services Receipt Inventory (CSRI) including use of hospital versus in-patient palliative EoL^d^ care and the use of informal care or services provided outside of the health care system (to be completed by caregivers) and modified to reduce overlap with Medicare data	✓	✓	✓
		Primary outcome expressed as cost per participant with a meaningful change in well-being or self-efficacy for the intervention compared with control	For patients and caregivers: EQ-5D and EQ-5D-5L (5 items)	✓	✓	✓
		Secondary outcomes expressed as cost per quality adjusted life year for the intervention compared with control	For patients and caregivers: Services Australia data—use of outpatient medical and pharmaceutical services	✓	✓	✓

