### Stage 3: Acceptability, Feasibility, and Scalability of FOCUSau (Objective 4)

Our approach is underpinned by a conceptual framework that highlights the link between acceptability, fidelity and feasibility, and potential implementability [66]. An investigation of fidelity will also inform internal validity and thus our interpretation of the effectiveness findings. If prospective acceptability, uptake and engagement with the intervention are moderate (based on conventional cutoff scores of 50%) [67,68], then FOCUSau is feasible to deliver in other settings; if participants receive and comprehend FOCUSau as designed (ie, fidelity is high), then the effectiveness findings will represent a valid test of the intervention; if participant retention and retrospective acceptability are high, then FOCUSau is likely to be maintainable; and if FOCUSau is cost-effective and additional workforce requirements are minimal, then the intervention is likely to be scalable. Acceptability is “the extent to which people receiving FOCUSau consider it to be appropriate, based on anticipated (prospective) or experienced (retrospective) cognitive and emotional responses to the intervention” [69]. Informed by a new and influential theoretical framework of acceptability [69], we will pilot test a questionnaire [44] to be administered at baseline and follow-up (T_0_ and T_2_). As acceptability is ideally assessed both quantitatively and qualitatively [36], a diverse subsample of participants (~30 dyads) will be recruited from the intervention group and be interviewed via videoconference immediately following the completion of FOCUSau (T_1_), to gain a greater insight into intervention acceptability, including potential for further enhancements. As for the uptake, we will document the recruitment process, including reasons for accepting or declining participation and examine the sociodemographic profile of dyads invited to participate in the trial, capturing our capacity to reach relevant populations (with lower socioeconomic status, cultural minorities, and from rural or remote locations). We will also use the aforementioned T_1_ interviews to explore barriers and enablers to uptake by dyads. Interview topic guides (1 for patients; a parallel guide for caregivers) will be informed by the TDF of behavior change [65]. Intervention fidelity encompasses whether the intervention is delivered and received as planned [70]. We will document communication between trial managers and participants, whether for technical problem-solving or for other reasons, to assess whether components have been added to FOCUSau as designed. Aspects of adherence (intervention as received) are built into the FOCUSau internet module and include a readily accessible “help” function. Dyads who experience problems with onboarding for the FOCUSau sessions will receive help from the trial manager via phone; they will confirm their presence and indicate whether they are using the computer or phone; dyads who exit an FOCUSau session before completion will be sent a reminder email or text message. Completion rates of individual FOCUSau sessions will be monitored.

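### The two responder-based cost-effectiveness ratios are to be estimated only if an undefined difference in outcomes is observed, although the cost-effectiveness hypothesis carries no such condition

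*Protocol article*

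**What the plan says.** All references are to the protocol article.

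- **Data Analysis, cost-effectiveness paragraph.** Costs come first and without condition: "costs will be reported as the mean costs of care per dyad in each arm of the study". The condition follows: "If a difference in outcomes is observed, as hypothesized, the incremental cost-effectiveness of FOCUSau compared with control will be estimated". It applies to two ratios, one for patients (emotional well-being) and one for caregivers (self-efficacy).
- **Research Aim and Hypotheses.** The economic hypothesis is unconditional: "FOCUSau will be cost-effective compared with the control group in terms of the incremental cost (change in health care use) per additional participant". Participants are counted there by whether they change meaningfully on each of the two primary outcomes.
- **Table 1, cost-effectiveness rows.** Cost per participant with a meaningful change is the primary economic outcome. The next row reads "Secondary outcomes expressed as cost per quality adjusted life year for the intervention compared with control". Neither row carries a condition.
- **Stage 3.** The scalability reasoning uses the economic result as a premise: "if FOCUSau is cost-effective and additional workforce requirements are minimal, then the intervention is likely to be scalable".

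**The concern.** The two ratios answer the economic hypothesis, yet whether they are estimated depends on the effectiveness data. There are three difficulties.

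1. **The trigger is not defined.** Two primary outcomes in two populations give four comparisons. The text does not say which of them must differ, in whom, or by how much. Whether to report could then be settled after the data are seen.
2. **The condition does not fit the question.** Failing to observe or to demonstrate a difference is not evidence of equal effect. Adoption depends on cost and effect together. For a self-administered digital programme whose effect on service use is being measured, a small gain at lower cost is a plausible and useful result. The rule would leave it unestimated.
3. **Reporting becomes selective.** If ratios appear only after a favourable result, the effects in them are on average larger than the truth.

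At stake are an answer to the stated cost-effectiveness hypothesis and the input to the Stage 3 premise.

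**Working it through.** **The plan's own figure.** The article gives no economic figure. The only stated number that bears on this point is 173 dyads per arm (Sample Size). With d = 0.375, two-sided α = .025 and 80% power:

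n = 2(z₀.₉₈₇₅ + z₀.₈₀)²/d² = 2(2.241 + 0.842)²/0.375² ≈ 136 per arm (137 by the t-test).

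So 173 is not reproduced from the stated inputs. The recruitment step is: 346/0.8 = 432.5, rounded up to 433. The mismatch is a separate matter and does not decide this point. I take 173 as the number analysed per arm, because the plan recruits 433 in order to keep 346.

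**Other inputs.** Planned effect 0.375 SD (Sample Size). Test level: "using a significance level of α=.025" (Data Analysis). Sidedness is not stated, and two-sided is assumed. The Sample Size section also says "H(1)0 is tested first at a significance level of 5" per cent, so that level is run as a variant.

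**Formulas.** SE = √(2/n). The boundary for a favourable significant result is c = z·SE, and k = (c − d)/SE. The probability that a ratio is reported is 1 − Φ(k). The mean effect among reported ratios is d + SE·φ(k)/(1 − Φ(k)).

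**Reading A: *observed* means significant.** For n = 173, d = 0.375 and α = .025:

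- SE = √(2/173) = 0.1075; c = 2.241 × 0.1075 = 0.241; k = (0.241 − 0.375)/0.1075 = −1.25
- P(reported) = 0.894, so no ratio in 1 − 0.894 = 10.6% of trials
- Mean reported effect = 0.397; 0.397/0.375 = 1.06

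**Reading B: any favourable difference suffices.** The same formulas apply with c = 0.

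True effects below 0.375 SD are assumptions, shown for range (n = 173 throughout):

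| True effect (SD) | A: P(reported) | A: reported/true | B: P(reported) | B: reported/true |
|---|---|---|---|---|
| 0.375 (planned) | 0.894 | 1.06 | 1.00 | 1.00 |
| 0.30 | 0.708 | 1.17 | 0.997 | 1.00 |
| 0.25 | 0.533 | 1.32 | 0.990 | 1.01 |
| 0.20 | 0.351 | 1.57 | 0.969 | 1.04 |

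**Variants at 0.375 SD under reading A.** At the 5% level, P(reported) is 0.937 and the factor 1.04. With 138 per arm (173 × 0.8, as if losses came out of the 173), they are 0.809 and 1.11. The plan's own allowance for losses argues against the 138 case.

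**Responder scale.** The denominator of each planned ratio is a difference in responders, not in means. A simulation of 20,000 trials, with responder cut-offs assumed at 0 and 0.42 SD, gave the same factors: 1.06 at 0.375 SD, 1.31 to 1.32 at 0.25 SD, and 1.56 at 0.20 SD.

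**Caregiver ratio.** Self-efficacy is tested only after a significant result on emotional well-being. If that sequence runs within caregivers and both true effects are 0.375 SD, the chance of no caregiver ratio under reading A lies between 10.6% and 2 × 10.6% ≈ 21%, depending on how the two outcomes correlate.

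**The case against.** The strongest reply has five parts.

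- **The text says *observed*, not *significant*.** Where the article means significance, as in the fixed-sequence rule, it says so. This stands. A reader might infer that the economic result hangs on the effectiveness test, but the words do not establish that. Against it, the phrase about the hypothesis points back to hypotheses tested at .025, so reading A is possible. If reading A is wrong, the trigger has no definition at all.
- **Not all of the economics is conditional.** This stands. Mean costs by arm are always reported, and cost per QALY is listed without condition. Objective 3 concerns types and costs of services and can be answered whatever the outcomes show. Neither item fills the gap, though. Arm costs alone are not cost-effectiveness, and the hypothesis is framed in meaningful changes, not QALYs.
- **The Stage 3 rule is only a sufficient condition.** It is not contradicted when no ratio exists. This also stands, but its premise could then not be assessed.
- **A ratio with a denominator near zero is unstable.** Some restraint in presenting it is reasonable. That is a reason to limit the display of the ratio, not the estimation of incremental cost and incremental effect.
- **The estimate within a given trial is unchanged by the rule.** This is correct. The overstatement arises across possible trials through selective reporting. It makes the cost per responder look too favourable only when incremental cost is positive.

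**Conclusion.** The point holds in a limited form. Two responder-based ratios depend on an undefined, data-dependent trigger, while the hypothesis and the primary economic outcome that they serve are stated without one. Followed as written, the plan could leave that hypothesis unanswered. This does not rest on how *observed* is read, although the size does. Under significance at two-sided .025, with 173 per arm and the planned 0.375 SD, about 11% of trials would report no ratio and the mean overstatement would be about 6%. If any favourable difference is enough, both are negligible at the planned effect.

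A reader might go further and infer that reported ratios would be badly inflated. Factors of 1.3 to 1.6 need both the significance reading and true effects of 0.25 to 0.20 SD, which the documents do not give. The main cost of the rule is the possible loss of the estimate. The primary effectiveness analysis is unaffected.

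**What to change.** Delete the condition in the cost-effectiveness paragraph of Data Analysis. State that incremental cost and incremental effect will be estimated for both populations whatever the primary tests show, with their joint uncertainty. Bootstrapping whole dyads is one way, since it keeps the correlation between cost and effect. Present the ratio itself only where it is interpretable, and say in advance what will be shown otherwise. The technical detail can sit in the analysis plan, and its absence from the article is not criticised here.

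The cost is a change of wording and a little extra analysis of data already scheduled at all three time points. The downside is that a ratio may be very imprecise when the effect is near zero.
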